### 2.10. Endpoints

-Invasive CRC: this is the main endpoint of the study and is defined as a colonic adenocarcinoma that invades the submucosa. We will not consider adenocarcinomas in situ and intramucosal carcinomas as invasive CRC.-Interval CRC: this is defined as the CRC detected between two organized surveillance (FIT or colonoscopy).-Mortality: we will collect the deaths and their cause (associated with CRC, associated with adverse effects or unrelated).-Colonic lesions: we will classify colonic lesions as advanced or not advanced. We will define advanced lesions as advanced adenomas (some of at least 10 mm, hairy histology or high grade dysplasia) or advanced serrated lesions (some of at least 10 mm or with dysplasia). The rest will be classified as not advanced.-Participation in the surveillance strategy: we will define three categories to evaluate the participation: non-participation, irregular and regular participation.-Adverse effects: adverse effects associated with surveillance are defined as complications that require hospitalization. Those related to the surgical treatment of benign colonic lesions will be also included as adverse effects.

### 2.11. Exit from the Study

Patients will leave the study due to death, CRC diagnosis, withdrawal of consent to participate or completion of the study period. At the end of the 10 years, patients assigned to group I will remain in the population-based CRC screening program. Patients in group II will continue to perform endoscopic surveillance according to the recommendations established by the existing CPG.

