### 2.2. Objectives

The main objective of our study is to compare the 10-year CRC incidence between patients undergoing endoscopic surveillance and patients participating in a population CRC screening program based on annual FIT determination. Additionally, we have defined the following as secondary objectives:
-To compare the diagnostic yield for CRC and advanced adenomas detection between both groups at a 3 year interval.-To evaluate the effect of the two surveillance strategies on the following variables: mortality (global and associated with CRC), colonic lesion detection, participation in the surveillance strategy, adverse effects, use of health resources and cost-effectiveness.-To determine the values and preferences of subjects with advanced adenomas resected endoscopically regarding the type of surveillance and the risk of CRC.

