### 2.12. Data Management

We will collect all the information in a database designed for this purpose. Regarding baseline data, we will include the inclusion and exclusion criteria, demographic information and the characteristics of the initially resected colonoscopies and polyps. We will also collect the questionnaires administered, the intervention information, the FIT rounds, all the colonoscopies performed and the appearance of the study endpoints in the database. The study requires the long-term follow-up of the patient, so it is possible that they could change their address. In this case, a pseudo-anonymized identification number will be used to determine the appearance of CRC and mortality, in accordance with the general data protection regulation (2016/679) and the Law on Protection of Personal Data and guarantee of digital rights (Organic Law 3/2018).

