### 2.15. Statistical Analysis

The primary analytical approach to the trial will follow the principle of intention to treat (ITT). We will compare the differences for each endpoint between the groups by calculating the incidence, incidence density, risk differences and applying the log-rank test. We will also perform an analysis per protocol to estimate the causal effect that would have been observed if all the people in the intervention arms had met.

For the analysis of the diagnostic yield at three years, we will compare the rates of CRC, adenoma and advanced serrated lesions detection using the risk ratio and relative risk. Logistic regression will be performed to adjust the risk ratio using age, sex, screening program and stratification as confusing variables.

We will also develop a cost–utility Markov model to evaluate the cost-effectiveness of CRC screening. The model will consider different health states based on the usual clinical progression of CRC. We will use the data obtained from this clinical trial, such as transition probabilities, sensitivity, specificity, incidence and mortality rates due to CRC. The EuroQol questionnaire (EQ–5D) [18] will be used to measure the utilities associated with the CRC.

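### CRC diagnosis is listed as an exit from the study, which conflicts with the CRC-mortality endpoint and with using the trial's own CRC death rates in the cost-utility model

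*Protocol article*

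**What the plan says.** Section 2.11 gives one list of exit events: "Patients will leave the study due to death, CRC diagnosis, withdrawal of consent to participate or completion of the study period". CRC diagnosis stands beside death and consent withdrawal without any distinction. No sentence says that data are still collected after an exit at diagnosis.

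Other sections need information from after a CRC diagnosis:

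- Section 2.2 sets as a secondary objective the effect on "mortality (global and associated with CRC").
- Section 2.10 defines the mortality endpoint: "we will collect the deaths and their cause (associated with CRC, associated with adverse effects or unrelated").
- Section 2.15 builds a Markov model from trial data, "such as transition probabilities, sensitivity, specificity, incidence and mortality rates due to CRC", and says that the EQ-5D "will be used to measure the utilities associated with the CRC".
- Section 2.15 also adopts intention to treat as the primary approach and applies the log-rank test to each endpoint.

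Section 2.12 describes a way to ascertain outcomes without contact. It follows a remark that patients may move house during long follow-up: "In this case, a pseudo-anonymized identification number will be used to determine the appearance of CRC and mortality".

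**The concern.** Apart from the rare case in which CRC is first recognised at death, a CRC death comes after a CRC diagnosis. If leaving the study ends data collection, patients leave just before they become at risk of the secondary endpoint. Both arms would then show close to no CRC deaths whatever the truth, and a reader could take that for reassurance.

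This matters because the design tolerates up to 1 percentage point more CRC in the FIT arm (sections 2.9 and 3). CRC mortality is the outcome that would show whether such an excess, or a later stage at diagnosis, costs lives.

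Two further consequences follow. In the all-cause log-rank comparison, censoring at CRC diagnosis is informative, because those patients have a higher risk of death, and it is unequal between arms if incidence differs. The Markov model would also lack trial data on survival after CRC, although section 2.15 says that CRC death rates come from the trial.

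**Working it through.** **Inputs.** From section 2.9: CRC incidence 1.24% in both arms, margin 1%, alpha 0.05, power 0.80 (the stated 0.8 is read as power), 1515 evaluable and 1894 recruited per arm, 20% dropout. From section 1: 39% of people with CRC in Spain die of it. Assumed here, because the documents give no figure: a CRC fatality of 10% to 20% for a surveilled cohort, and 10-year all-cause mortality of 3%, 5% or 8%.

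**The plan's own figure.** n = (z₀.₉₅ + z₀.₈₀)² × 2p(1 − p) / δ² = (1.645 + 0.842)² × 2 × 0.0124 × 0.9876 / 0.01² ≈ 1514.3, rounded up to 1515 per arm. 1515 / 0.80 = 1893.75, so 1894. Both figures reproduce, with alpha taken as one-sided. Nothing in this point changes them.

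**Patients who exit at CRC diagnosis.**
- Evaluable: 0.0124 × 3030 = 37.6
- Recruited: 0.0124 × 3788 = 47.0

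**Eventual CRC deaths after exit** (an upper bound on those within 10 years, since the timing is not given).

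| Fatality | 3030 evaluable | 3788 recruited |
|---|---|---|
| 10% (assumed) | 3.8 | 4.7 |
| 20% (assumed) | 7.5 | 9.4 |
| 39% (section 1, national) | 14.7 | 18.3 |

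Under the literal rule, nearly all of these are lost.

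**Effect on all-cause mortality.** Share of deaths lost = (0.0124 × fatality) / all-cause mortality.
- Fatality 39%: 18.3 of 113.6 deaths (16%) at 3% mortality, 18.3 of 189.4 (10%) at 5%, and 18.3 of 303.0 (6%) at 8%.
- Fatality 10%: 0.00124 / 0.03 = 4% down to 0.00124 / 0.08 = 2%.

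Deaths from other causes after a CRC diagnosis would add a few. The other 98.8% of patients (100% − 1.24%) are expected to have no CRC, and the rule does not touch their deaths.

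**Imbalance at the margin.** If FIT-arm incidence were 1.24% + 1% = 2.24%, exits at diagnosis would be 0.0224 × 1894 = 42.4 against 0.0124 × 1894 = 23.5, an excess of 18.9. At 10% to 39% fatality that means 1.9 to 7.4 extra eventual CRC deaths in the FIT arm that the mortality comparison would not see.

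**Does leaving the study mean only leaving surveillance?** Three places bear on this.
- Section 2.8 already has its own rule for group II: surveillance colonoscopies are not done once a study endpoint is reached. The exit list would not be needed for that purpose.
- Section 2.11 counts completion as an exit, yet says that both groups then carry on with screening or endoscopic surveillance. There, leaving the study is not the end of surveillance.
- Section 2.12 ties the identifier to patients who change address and does not extend it to those who left at diagnosis.

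**The case against.** The best defence is that section 2.11 can be read as ending the surveillance strategy only. Section 2.10 promises to collect deaths and causes without restriction, and section 2.12 shows that mortality can be found without active participation. Nothing forbids collecting deaths after diagnosis. A condensed article may also leave such detail to the full protocol.

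Part of this stands. The text is not a prohibition, and the identifier shows that the data could be recovered. But the lenient reading is nowhere stated and fits the surrounding sections poorly. The point also rests on a stated rule that clashes with stated endpoints, not on missing detail.

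Three stronger inferences are tempting, and the documents do not support them.

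- **That overall mortality cannot be measured, or omits exactly the deaths surveillance could affect.** Most deaths will be in patients without CRC. Section 2.10 also lists deaths linked to adverse effects, which remain observable unless a CRC diagnosis came first.
- **That CRC utilities cannot be obtained.** Section 2.15 does not say who completes the EQ-5D or when. Completion around the time of diagnosis would fit the text, and questionnaire timing is ordinary full-protocol detail.
- **That 15 to 18 CRC deaths would be lost.** The 39% is a national figure for all CRC. Section 1 itself credits screening with earlier detection and lower mortality, so it is probably too high for this cohort.

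It is also fair to say that so few CRC deaths would give an imprecise comparison even if all were captured, and that higher incidence would still show in the primary endpoint.

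**Conclusion.** The conflict is real and of moderate importance. As written, the exit rule in section 2.11 contradicts the CRC-mortality objective and endpoint and the stated source of the model's CRC death rates. If it is followed literally, nearly all CRC deaths among about 38 to 47 expected cases go unrecorded: roughly 4 to 9 eventual deaths at the assumed 10% to 20% fatality, or 15 to 18 at the national 39%, with an unknown share inside 10 years. All-cause mortality would lose a minority of its events, about 2% to 16% under the assumptions above, through informative censoring.

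The conclusion assumes that leaving the study ends data collection, which is the plain sense of the list but is not spelled out. The primary endpoint is unaffected, because exit coincides with the primary event, and the sample size is unaffected too. For that reason this is a correction to a secondary endpoint and to model inputs, not a threat to the main conclusion.

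**What to change.** Reword section 2.11 so that a CRC diagnosis ends study surveillance and follow-up time for the primary endpoint, but not follow-up for vital status. The change concerns data collection only.

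- **Section 2.12:** ascertain vital status and cause of death to 10 years from randomisation for all randomised patients, using the identifier for everyone and not only for those who move, subject to consent.
- **Section 2.15:** analyse all-cause and CRC mortality by intention to treat, without censoring at CRC diagnosis.
- **EQ-5D:** if utilities for CRC states are to come from trial patients, the exit rule must also allow collection after diagnosis.

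The cost is a wording change, notice to the ethics committee (section 2.14), a check that the consent covers linkage for everyone, and a small amount of extra follow-up data for about 47 patients. It is best made early: deaths can be recovered later by linkage where consent allows, but EQ-5D responses missed after diagnosis cannot. The CRC-mortality comparison will still rest on few events and should be reported as such.

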### 2.12. Data Management

We will collect all the information in a database designed for this purpose. Regarding baseline data, we will include the inclusion and exclusion criteria, demographic information and the characteristics of the initially resected colonoscopies and polyps. We will also collect the questionnaires administered, the intervention information, the FIT rounds, all the colonoscopies performed and the appearance of the study endpoints in the database. The study requires the long-term follow-up of the patient, so it is possible that they could change their address. In this case, a pseudo-anonymized identification number will be used to determine the appearance of CRC and mortality, in accordance with the general data protection regulation (2016/679) and the Law on Protection of Personal Data and guarantee of digital rights (Organic Law 3/2018).

### 2.13. Study Monitoring

An independent monitoring and security committee will be created externally to review the progress of the study and ensure it is carried out according to the ethical rules. The committee members will be appointed by the principal investigators and will not have any role in the progression of the study. Additionally, internal rules will be established in the database to identify inconsistencies in the information included. A calendar of audits of the archive information will be also scheduled in each of the centers.

### 2.14. Ethical and Legal Aspects

The study was designed according to the Declaration of Helsinki, in the Council of Europe Convention on Human Rights and Biomedicine, and according to the Spanish legislation in the field of biomedical research, the protection of personal data and bioethics. Specifically, the management of both the data collected and the medical records will comply at all times with the requirements of the general data protection regulation (2016/679) and Organic Law 3/2018 of Protection of Personal Data and guarantee of digital rights. Ethical approval was obtained from the Clinical Research Ethics Committee of Galicia, Spain (2020/053). Informed consent will be obtained from all study participants. Any possible protocol modification will be communicated to the ethical committee and to all relevant parties.

### 2.15. Statistical Analysis

The primary analytical approach to the trial will follow the principle of intention to treat (ITT). We will compare the differences for each endpoint between the groups by calculating the incidence, incidence density, risk differences and applying the log-rank test. We will also perform an analysis per protocol to estimate the causal effect that would have been observed if all the people in the intervention arms had met.

For the analysis of the diagnostic yield at three years, we will compare the rates of CRC, adenoma and advanced serrated lesions detection using the risk ratio and relative risk. Logistic regression will be performed to adjust the risk ratio using age, sex, screening program and stratification as confusing variables.

We will also develop a cost–utility Markov model to evaluate the cost-effectiveness of CRC screening. The model will consider different health states based on the usual clinical progression of CRC. We will use the data obtained from this clinical trial, such as transition probabilities, sensitivity, specificity, incidence and mortality rates due to CRC. The EuroQol questionnaire (EQ–5D) [18] will be used to measure the utilities associated with the CRC.

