### 2.9. Sample Size Calculation

We designed the study on the basis that CRC incidence in the two groups will be 1.24% [16], with a 1:1 ratio between both groups and a non-superiority limit in 1% [17]. Assuming a 0.8 B error and an alpha error of 0.05, 1515 patients should be included in each group. Accounting for an estimated dropout percentage of 20%, it is necessary to recruit 1894 patients in each group, leading to a total of 3788 subjects in the study. This sample size calculation was carried out with the statistical program Ene 3.0.

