## 3. Discussion

This trial was designed to evaluate the potential of annual FIT for CRC surveillance of patients with advanced colonic lesions instead of surveillance colonoscopy. We will evaluate a different screening strategy based on an annual FIT test using a low fecal hemoglobin threshold and colonoscopy in positive cases. We selected a 10-year period according to previous recommendations for surveillance after adenoma resection [19]. Additionally, the main goal of our study is the prevention of the disease, which is why a 10-year period is adequate to evaluate CRC incidence. On the other hand, we think the CRC incidence in the FIT based strategy is non-superior to colonoscopy surveillance and in order to establish the 1% margin, we used the magnitude of benefit that typical members of the population would value to opt for screening [17]. Additionally, we chose a superior margin to other ongoing trials, because a superior CRC incidence would be outweighed by a reduction in the cost of surveillance, the number of colonoscopies and the rate of associated complications [20].

The diagnostic accuracy of FIT is high in terms of the CRC detection rate in CRC screening programs [21]. Hence, its accuracy can reach 100% sensitivity and 90–94% specificity for CRC detection in CRC-screening programs and evaluation of symptomatic patients [22]. On the contrary, FIT has a limited diagnostic accuracy for advanced colonic lesion at a single determination. In asymptomatic Spanish subjects recruited at the hospitals included in our study, a single FIT determination detects 31% and 21% of advanced adenomas at the 10 µg Hb/g and 20 µg Hb/g of faeces thresholds, respectively, with a specificity higher than 90%. There are several characteristics of the adenomas associated with a positive FIT: number, location, morphology and size [21]. However, the strength of an FIT-based CRC screening is that it is based on periodic (annual or biennial) determination [23]. A recent British study shows that the sensitivity for CRC and advanced adenomas increases with each annual FIT round [14]. Furthermore, the threshold used can be tailored according to colonoscopy capacity and long-term objectives. However, not all the adenomas will progress to a CRC, and the aim of a surveillance strategy is to detect only the adenoma that will progress to CRC in the next surveillance period.

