On the other hand, the evidence regarding the benefits of endoscopic surveillance in high-risk lesions is limited to cohort studies. In a study published by Cottet et al., in 2012 [24], the standardized incidence ratio (SIR) was 1.10 (95% CI: 0.62–1.82) and 4.26 (95% CI: 2.89–6.04) in those patients with and without colonoscopy follow-up, respectively. Atkin et al., also showed, in a study including 12,000 patients with high-risk lesions (1–2 adenomas ≥10 mm or 3–4 adenomas <10 mm), that performing at least one endoscopic surveillance reduces the incidence of CRC (HR 0.57, 95% CI: 0.40–0.80). However, this risk reduction was limited to a subgroup of patients: low-quality colonoscopy, large (≥20 mm), high-grade dysplasia and proximal adenomas [12]. In this respect, the available guidelines recommend performing baseline colonoscopy with a full exploration of the colonic mucosa and resection of all detected polyps [9,11,12]. CRC detection during surveillance depends not only on the characteristics of the polyps but also on the endoscopist’s technical ability. A recently published Polish study reveals that long-term risk of CRC is increased (HR 2.69, 95% CI: 1.62–4.47) if baseline colonoscopy is performed by low-performing endoscopists (adenoma detection rate <20%) [25]. In this sense, Spanish CRC screening programs initiate surveillance after a complete evaluation of colonic mucosa and resection of colonic lesions. Furthermore, they perform a continuous control of the endoscopist quality indicators [26]. The increased quality of the baseline exploration produces a stage migration. On one hand, the number of patients for which we recommend endoscopic surveillance is increasing. On the other hand, the most recently published articles showed a lower-than-expected long-term CRC incidence. This is an additional justification for our clinical trial [11].

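### Section 2.15 adjusts a risk ratio by logistic regression without naming the step that turns the model's odds ratio into a risk ratio (secondary 3-year yield analysis)

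*Protocol article*

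**What the plan says.** The 3-year yield is a secondary objective. Section 2.2 words it as "To compare the diagnostic yield for CRC and advanced adenomas detection between both groups at a 3 year interval". Section 2.15 sets the measure: "we will compare the rates of CRC, adenoma and advanced serrated lesions detection using the risk ratio and relative risk". Risk ratio and relative risk are two names for one quantity, so a single measure has been listed twice.

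The next sentence gives the adjusted analysis: "Logistic regression will be performed to adjust the risk ratio using age, sex, screening program and stratification as confusing variables". The article does not mention an odds ratio, a log-binomial or Poisson model, or a standardisation step. Earlier in section 2.15, incidence and risk differences are planned for every endpoint.

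**The concern.** The measure and the model do not match as written. Exponentiating the treatment coefficient of a logistic model gives an odds ratio conditional on the covariates. That is close to a risk ratio only when the outcome is rare or the arms barely differ. An analyst who follows the text literally would print an odds ratio in a column headed adjusted risk ratio, next to a crude figure that really is a risk ratio.

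The design makes a difference in yield plausible. Everyone in Group II is scheduled for a colonoscopy at three years (section 2.8), whereas Group I patients have one only after a FIT at or above the cut-off (section 2.7). If FIT finds fewer lesions, the mislabelled figure would overstate its shortfall. Part of any move from crude to adjusted would then be a change of scale and not an effect of the covariates.

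**Working it through.** **The plan's own figure.** The article gives no number for the yield analysis. Its only calculated figure is the primary sample size (section 2.9), which reproduces with a one-sided alpha of 0.05 and power of 0.8:

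n = (1.645 + 0.842)² × 2 × 0.0124 × 0.9876 / 0.01² = 6.183 × 244.92 ≈ 1514.3, so 1515 per arm. Then 1515 / 0.8 = 1893.75, so 1894.

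Nothing in it depends on the yield model.

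**Odds ratio against risk ratio.** Let p0 be the 3-year detection risk with colonoscopy (Group II) and p1 the risk with FIT (Group I). Ratios are FIT over colonoscopy.

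- RR = p1 / p0
- OR = [p1/(1 − p1)] / [p0/(1 − p0)] = RR × (1 − p0)/(1 − p1)

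If p1 < p0, the last factor is below 1, so the OR is further from 1 than the RR. This direction needs no assumption about frequency; the size does.

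**Inputs.** For CRC, section 2.9 assumes 1.24% over ten years; cumulative risk at three years cannot be higher. No yield for adenomas or advanced adenomas is given, so the rates below are assumptions. The nearest figure is in the Discussion, where an adenoma detection rate under 20% marks a low-performing endoscopist. That concerns baseline colonoscopy and is only indirect evidence that adenomas as a whole are not rare.

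| Case | p0 | p1 | RR | Factor (1 − p0)/(1 − p1) | OR | OR below RR by |
|---|---|---|---|---|---|---|
| CRC, illustrative RR 0.5 | 1.24% | 0.62% | 0.500 | 0.9876/0.9938 = 0.994 | 0.497 | 0.6% |
| Assumed, less common lesion | 15% | 8% | 0.533 | 0.85/0.92 = 0.924 | 0.493 | 7.6% |
| Assumed, common lesion | 30% | 15% | 0.500 | 0.70/0.85 = 0.824 | 0.412 | 17.6% |
| Assumed, very common lesion | 40% | 15% | 0.375 | 0.60/0.85 = 0.706 | 0.265 | 29.4% |

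**Range for common outcomes.**

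| p0 | OR when RR = 0.5 | OR when RR = 0.7 |
|---|---|---|
| 20% | 0.444 | 0.651 |
| 30% | 0.412 | 0.620 |
| 40% | 0.375 | 0.583 |
| 50% | 0.333 | 0.538 |

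The OR is 11–33% below an RR of 0.5 and 7–23% below an RR of 0.7.

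**Does the repair work?** One data set of 400,000 was simulated with 1:1 allocation, assumed effects of sex, stratum and age, and a colonoscopy-arm risk of 0.4988:

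- crude RR: 0.557
- exponentiated logistic coefficient: 0.375
- RR standardised from the same logistic model: 0.557
- modified Poisson RR: 0.557

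The crude OR follows from the identity: p1 = 0.557 × 0.4988 = 0.278, so OR = 0.557 × 0.501/0.722 ≈ 0.386. Most of the move from 0.557 to 0.375 is therefore the change of scale. The small remainder (0.386 to 0.375) is non-collapsibility. Both repairs return the measure the text promises.

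**The case against.** Four points can be made in the plan's favour.

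- **Logistic regression can deliver a risk ratio.** Standardising its predictions does so, as the simulation shows, and the full protocol or SAP may contain that step. This stands against any claim that the model is unusable. It does not clear the text, which links the model directly to the risk ratio with nothing between.
- **It may be a translation slip.** The article uses odd terms elsewhere: confounders are called confusing, and power of 0.8 is given as a B error. If the first half of "detection using the risk ratio and relative risk" was meant to be odds ratio, both sentences make sense and one word cures them. This is plausible but cannot be shown from the article, and the measure would still be misnamed.
- **The frequencies are not documented.** A reader might infer that advanced adenomas are common at surveillance, so that the distortion for the section 2.2 objective is large. The article does not support that. It gives no 3-year yield, and at an assumed 15% against 8% the gap is about 8%. The larger gaps belong to any-adenoma detection, and then only at the assumed rates.
- **There are safeguards.** The crude risk ratio and the risk differences are already planned, so a reader could see the absolute contrast and a mismatch of scale. With 1:1 randomisation little confounding is expected, so the fear that the gap will be taken for confounding is speculative. This stands and lowers the weight of the point.

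**Conclusion.** The mismatch is real and stated in the text: the risk ratio is promised, the model named has an odds ratio as its coefficient, and no conversion is given. The direction is certain whenever the arms differ, because the odds ratio is further from 1. The size depends on detection rates that the article does not give. It is under 1% for CRC, about 8% at an assumed 15% against 8%, and about 18% at an assumed 30% against 15%. It is therefore material only for common outcomes such as any adenoma. For advanced serrated lesions it cannot be sized, as no frequency is given.

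Two stronger readings are not supported: that logistic regression cannot yield an adjusted risk ratio, and that the trial's main conclusion is at risk. The point concerns covariate adjustment of a secondary endpoint. The primary 10-year CRC comparison, the margin and the sample size are untouched.

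**What to change.** Replace the adjustment sentence in section 2.15 with one of the following, and carry it into the SAP.

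- **If a risk ratio is intended:** *Adjusted risk ratios for 3-year detection will be obtained by standardisation from the logistic model, with the four covariates already listed.* Modified Poisson regression with robust variance is an equally good alternative. Name one of the two in advance.
- **If an odds ratio was intended:** say that logistic regression gives an adjusted odds ratio, and label it so in every table.

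In either case, remove the duplication of risk ratio and relative risk. No risk difference need be added, since section 2.15 already plans one for each endpoint.

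The cost is one or two sentences, with no new data, no change of covariates and no effect on design or sample size.
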